### Randomization

#### Allocation to Interventions

For the initial 4-week pilot trial, a computer-generated random sequence will be used to randomize participants to 1 of the 2 study arms. Stratification (eg, by age, sex, or symptom severity) or block randomization may be considered for the subsequent MRTs based on analysis from the preceding trials. A study statistician will generate the allocation sequences, and participants will be assigned to study arms automatically after they pass the web-based eligibility screen, review the study procedures, and complete the baseline study questionnaires; no direct involvement by study team members is required for study arm assignment. Criteria for discontinuing or modifying allocated interventions are described in Multimedia Appendix 1.

#### Blinding

Study team members involved in outcome assessment and data analysis will not be blinded to participants’ intervention assignment because (1) the primary proximal outcomes related to immediate app engagement will be collected automatically and in real time throughout each trial and (2) the study outcomes will not be analyzed until a given trial is complete. Trial participants cannot definitively be blinded to their intervention assignment because the notification experience within Wysa for Chronic Pain will differ between the 2 intervention arms. Nevertheless, all participants will receive the same Wysa for Chronic Pain therapeutic content, participants will not explicitly be notified which study arm they are assigned to, and participants in the intervention arm with JITAIs will not necessarily be aware when a notification (or lack thereof) from Wysa for Chronic Pain is related to a JITAI under investigation.

### Interventions

#### Wysa for Chronic Pain

The overarching digital intervention is Wysa for Chronic Pain, developed by Wysa for mobile devices (Multimedia Appendix 1). The general Wysa platform delivers cognitive behavioral therapy, dialectical behavioral therapy, motivational interviewing, mindfulness training, deep breathing, and sleep tools (eg, meditations, sleep hygiene education [29,30]) through an artificial intelligence–based chatbot that uses a combination of rule-based decision-making, natural language understanding, and large language models to facilitate maximally nuanced, personalized conversations. Wysa for Chronic Pain also specifically delivers therapeutic content related to behavioral activation and pain acceptance (ie, “acknowledging that one has pain, giving up unproductive attempts to control pain, acting as if pain does not imply disability, and committing one’s efforts toward living a satisfying life despite pain”; Figure 3) [50-53]. It uses push notifications to encourage user engagement and also allows for independent exploration of self-care tools by users. The version of Wysa for Chronic Pain that will be tested in these trials is fully automated.

**Figure 3 figure3:**
[figure not shown]
Screenshots of Wysa for Chronic Pain.

#### JITAIs Descriptions

Multiple JITAIs will be tested in the trials. Table 1 describes the JITAIs that will be tested in the first trial, but the final plan for each subsequent trial will be refined based on findings from the preceding trials and semistructured interviews. Each proposed JITAI in Table 1 involves the delivery of one or more push notifications to the participant. The notifications are intended to improve engagement in numerous ways, such as directing a user to a relevant therapeutic tool, adjusting the Wysa for Chronic Pain experience and frequency of scheduled notifications in order to meet the user’s demonstrated preferences and to reduce notification fatigue, and increasing the frequency of scheduled notifications when mental health symptoms have recently worsened.

**Table 1 table1:** Description of initial just-in-time adaptive interventions (JITAIs) to be tested in the microrandomized trials.

JITAI name	Purpose	Decision rule: tailoring variables and cut points	Decision rule: intervention^a^
Onboarding	Increase onboarding completion rates	If the user downloaded the app but did not complete onboarding within 24 hours of download	Then, send a notification that encourages the user to finish onboarding. The notification directs the user back to the onboarding screen. When possible, the notification is personalized based on information the user shared thus far during onboarding.
Short disengaged	Motivate a user to engage using messages or content that resonates with the user	If no app engagement for 24 hours	Then, send a personalized notification regarding a challenge the user endorsed at onboarding or during a previous conversation. The notification directly opens to a relevant tool.
Long disengaged	Respect that users’ preferred or needed frequency of engagement may fluctuate based on symptom severity and life events	If no app engagement for 7 days	Then, send an “FYI^b^ or opt back in”^c^ notification, and stop all notifications for 3 days. After 3 days, send a notification with a tool that was previously helpful or that has not been used yet but should be relevant based on challenges reported at onboarding. Then resume the previous notification schedule.
AM check-ins only	Personalize push timing to users’ demonstrated preferences	If no engagement with PM check-ins but ≥1 engagement with AM check-ins within the last 7 days	Then, send an “FYI or opt back in” notification, stop daily “PM check-in” notifications, and move the “activity tracking and mood reflection” task to the AM check-ins.
PM check-ins only	Personalize push timing to users’ demonstrated preferences	If no engagement with AM check-ins but ≥1 engagement with PM check-ins within the last 7 days	Then, send an “FYI or opt back in” notification, stop daily “AM check-in” notifications, and move the “activity scheduling and planning” task to the PM check-ins.
Sporadic engagement only	Personalize push timing and content to users’ demonstrated preferences (eg, engagement only during pain or mood symptom flares)	If no engagement with AM or PM check-ins, but ≥1 user-led engagement within the last 7 days	Then, send an “FYI or opt back in” notification, and stop daily “AM check-in” and “PM check-in” notifications. Instead, each day, send a single personalized notification that directs the user to a tool that was previously helpful or that has not been used yet but should be relevant based on challenges the user reported at onboarding.
Mental health flare^d^	Offer increased support when most needed	If PHQ-4^e^ score worsens compared to the preceding PHQ-4 score, and the user’s current push notification frequency is less than twice daily	Then, send an “FYI or opt out” notification, and increase notification frequency back to twice daily (ie, AM and PM check-ins).

^a^For the “onboarding” and “mental health flare” JITAIs, the intervention will be delivered immediately after the decision rule cut points are met. For all other JITAIs, the intervention will be sent after a strategic delay. If the user’s previous 3 engagement events with the app are within the same 6-hour interval of the day, the initial notification of the intervention will be sent at the time of day equal to the average of the user’s last 3 engagement events (ie, when the user has historically been more likely to engage). Otherwise, the notification will be sent at the last time of day the user entered the app.

^b^FYI: for your information.

^c^If the “opt back in” or “opt out” option is selected, the rest of the intervention is not delivered, the countdown clock for the decision rule resets, and a single personalized notification is sent that directs the user to a tool that was previously helpful or that has not been used yet but should be relevant based on challenges the user reported at onboarding.

^d^The “mental health flare” JITAI overrides any engagement-related JITAIs, which would otherwise reduce the frequency of push notifications to the user.

^e^PHQ-4: Patient Health Questionnaire-4, a 4-item measure to assess depression and anxiety symptom severity [54,55]. Users are prompted to complete the PHQ-4 once weekly as part of a weekly assessment and progress report.

Among participants in the “Wysa for Chronic Pain with JITAIs” intervention arm for each trial, each time they meet prespecified criteria per the JITAIs’ decision rules, they may receive the JITAI. In the initial 4-week pilot trial, they will receive the respective JITAIs described in Table 1 each time they meet the prespecified criteria. In the subsequent MRTs, they will be randomized to receive the respective JITAI, a variation of the JITAI (eg, different timing or content), or no JITAI at all. When the prespecified criteria are not met, participants will not receive a JITAI-related notification or any JITAI-related interventions. Several JITAIs are anticipated to be tested simultaneously in each MRT.

#### Concomitant Care

Participants will not be restricted from engaging in any concomitant care during the trial, including mental health or chronic pain treatments. Participants will be asked to self-report whether (and what types of) medication they take for their mental health or pain at baseline, and they will be asked whether and how their medication regimens have changed at each follow-up time point. They will also be asked to report whether they had any pain procedures or psychiatry, counseling, or physical therapy visits during each follow-up period.

### Outcomes

The purpose of each JITAI is to increase engagement with Wysa for Chronic Pain by improving usability. Therefore, the outcomes of greatest importance in these randomized trials are the proximal outcomes related to engagement (Table 2). All proximal engagement outcomes will be collected automatically for all participants through Wysa platform’s established infrastructure, regardless of whether participants complete follow-up study questionnaires.

**Table 2 table2:** Proximal outcomes for each of the initial just-in-time adaptive interventions (JITAIs) to be tested in the microrandomized trials.

JITAI name			Proximal outcomes		Outcome type		Target engagement time interval	
Onboarding			Completion of onboarding		Binary		24 hours	
**Short disengaged**								24 hours
	Primary outcome	Any engagement^a^		Binary				
	Secondary outcome	Content engagement^b^		Continuous				
**Long disengaged**								4 days
	Primary outcome	Any engagement		Binary				
	Secondary outcome	Content engagement		Continuous				
**AM check-ins only**								7 days
	Primary outcome	Daily engagement^c^ with the “activity tracking and mood reflection” task		Continuous				
	Secondary outcome	Change in content engagement compared to the 7 days preceding		Continuous				
**PM check-ins only**								7 days
	Primary outcome	Daily engagement with the “activity scheduling and planning” task		Continuous				
	Secondary outcome	Change in content engagement compared to the 7 days preceding		Continuous				
Sporadic engagement only			Change in content engagement compared to the 7 days preceding		Continuous		7 days	
Mental health flare			Change in content engagement compared to the 7 days preceding		Continuous		7 days	

^a^“Any engagement” is operationalized as opening the app during the target engagement time interval.

^b^“Content engagement” is operationalized as the total number of tools, conversations, and check-ins the user engaged with during the target engagement time interval.

^c^“Daily engagement” is operationalized as the total number of days the user completed the task of interest during the target engagement time interval.

Distal clinical outcomes will be collected through a self-reported electronic questionnaire. The primary distal outcome will be the Patient Health Questionnaire Anxiety and Depression Scale (PHQ-ADS) [56,57], which is a combination of the Patient Health Questionnaire (PHQ-9) and Generalized Anxiety Disorder-7 (GAD-7) [47,48]. This single measure captures symptoms from both mental health conditions, which Wysa for Chronic Pain is primarily intended to address. Of note, values of these distal clinical outcomes will be the same across all JITAIs tested. In this formative project, analysis of changes in clinical outcomes from baseline to the final follow-up time point will not directly shed insight into the clinical effectiveness of each JITAI but rather will provide insight into the effectiveness of the entire Wysa for Chronic Pain intervention as it is iteratively refined between randomized trials.

In accordance with the National Institute of Mental Health’s (NIMH) experimental therapeutics approach, measures of clinical mechanisms of action will also be collected electronically through self-report (Table 3). We have previously reported signals of mediation by the 3 proposed clinical mediators of behavioral activation, pain acceptance, and sleep quality [53].

**Table 3 table3:** Operationalization of mediators and outcomes.

Construct					Measure

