**Methods:**

Using a mixed methods, human-centered design approach and a series of randomized trials, we will test and iteratively refine just-in-time adaptive interventions (JITAIs) that are designed to increase engagement with a digital mental health intervention. Participants will be aged 45 years or older, endorse at least moderately severe depression or anxiety symptoms (Patient Health Questionnaire-9 or Generalized Anxiety Disorder-7 score ≥10), and have coexisting chronic pain (ie, pain on most days or every day in the past 3 months), and live in the United States. In this open, web-based trial, participants will all receive Wysa for Chronic Pain (by Wysa), which uses a behavioral activation framework and encourages users to work toward pain acceptance. The fully automated intervention also includes cognitive behavioral therapy, mindfulness, and sleep tools, among others. In each trial, participants will be randomized during a maximum 12-week study period to receive versus not receive novel JITAIs that are intended to reduce navigation burden and improve usability (and subsequent engagement and clinical effectiveness). The JITAIs are being designed with iterative user feedback, guided by the Discover, Design/Build, and Test framework and the Behavioral Intervention Technology model. The proximal outcome for each JITAI is related to engagement with Wysa for Chronic Pain after JITAI delivery (compared to when no JITAI is delivered). The primary distal clinical outcome is the Patient Health Questionnaire Anxiety and Depression Scale. Based on statistical analysis that is triangulated with qualitative feedback from a subsample of trial participants, the JITAIs will be iteratively refined and retested in subsequent microrandomized trials until retesting of refined adaptations no longer yields meaningful improvement in immediate engagement or a maximum of 5 total trials have been completed.

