### Goal of This Study

We are conducting a large-scale, 3-phase project using human-centered design and the Discover, Design/Build, and Test (DDBT) framework to optimize an existing digital mental health intervention (Wysa for Chronic Pain) for middle-aged and older adults with depression or anxiety and coexisting chronic pain [43]. In the first project phase, we conducted semistructured interviews and usability testing among this target user population. During that process, novel JITAIs for Wysa for Chronic Pain were developed using the Behavioral Intervention Technology (BIT) model [36,44], which links established behavior change strategies with technology-related design and implementation factors—for example, timing, medium (text, audio, or video), and complexity of intervention delivery—that affect engagement and subsequent effectiveness of a digital health intervention [44,45].

This study protocol outlines the second project phase. In a series of traditional and microrandomized trials (MRTs) that are interspersed with qualitative feedback from a subgroup of trial participants, the goal of this study is to test and optimize the effectiveness of the novel JITAIs to increase engagement among middle-aged and older adults with Wysa for Chronic Pain. The central hypothesis is that incorporating these JITAIs will increase engagement with Wysa for Chronic Pain by improving usability and, subsequently, will improve depression and anxiety symptoms in this population. After completion of this phase, the third project phase will be a pragmatic, hybrid type 1 effectiveness-implementation trial during which the final JITAIs will be fully integrated into the Wysa for Chronic Pain user experience.

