## Methods

### Study Design and Setting

In this remote, single-site, mixed methods study, we will conduct a series of randomized trials interspersed with semistructured interviews (Figure 1). The first trial will be a traditional 4-week, 2-arm randomized controlled trial in which participants receive “Wysa for Chronic Pain with JITAIs” or “Wysa for Chronic Pain without JITAIs.” The primary purpose of this first trial is to obtain preliminary information regarding the frequency that (1) the prespecified criteria (ie, decision rules) are met for each JITAI and (2) participants engage with each JITAI. These quantitative data, coupled with qualitative data from semistructured interviews with a subgroup of trial participants, will guide the final design (and particularly the initial randomization probabilities) of a subsequent 12-week MRT. MRTs were developed as a novel study design by Susan Murphy and colleagues [46] to rigorously study JITAIs. In an MRT, each participant is repeatedly randomized multiple times during the course of the trial. For example, randomization can be related to (1) receiving one versus another JITAI (or none at all) when fixed prespecified criteria are met or (2) variations in the prespecified criteria or delivery of a JITAI (eg, timing for the decision rule, timing of JITAI delivery, JITAI language, etc). In this way, both between-participant and within-participant comparisons can be made, which increases the efficiency of the trial. Furthermore, time-varying effects of a JITAI can be studied with an MRT, for instance, to evaluate a JITAI’s impact on engagement during the first day of app use (when engagement is typically high) compared to the tenth week of app use (when engagement is typically lower) [46].

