**Figure 1 figure1:**
[figure not shown]
Study design. JITAI: just-in-time adaptive intervention; MRT: microrandomized trial; RCT: randomized controlled trial.

We anticipate performing 2-4 MRTs as part of this study, depending on opportunities that we identify for continued JITAI refinement based on our quantitative and qualitative findings after each trial, within the limitations of time and budget constraints. Each MRT will include 2 arms (Figure 2). Participants in the “Wysa for Chronic Pain with JITAIs” intervention arm will be randomized every time they meet prespecified criteria (ie, decision rules) for the JITAIs under investigation, whereas participants in the “Wysa for Chronic Pain without JITAIs” control arm will never receive JITAIs, regardless of whether they meet the prespecified criteria. Inclusion of a control arm in each trial will facilitate accounting for time-varying factors (eg, refinements to the Wysa for Chronic Pain user experience that are unrelated to the JITAIs) and enable additional secondary analyses.

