#### Additional Analyses

In a secondary analysis, we will evaluate whether the JITAIs’ effects on engagement vary with time based on the week of the study. The distal clinical outcomes in Table 3 at weeks 4, 8, and 12 will be analyzed using mixed-effects models to test for moderating effects of participant characteristics—for example, age group (middle-aged: 45-64 years vs older adult: 65 years or older), sex, race and ethnicity, depression or anxiety severity [6], and chronic pain duration—and engagement with the Wysa app (ie, total dose, duration, and content) by including these as interaction terms.

We will also estimate optimal JITAIs for the distal clinical outcomes using methods from reinforcement learning [65,66], and we will evaluate the appropriateness of engagement as a surrogate for long-term clinical outcomes by comparing the performance of an optimal JITAI that targets engagement with one that is optimized for the distal clinical outcomes of interest.

Other secondary analyses will include development of models that predict the likelihood that a user will disengage with Wysa for Chronic Pain; descriptive analyses of the estimated optimal JITAI (eg, if, when, and for whom a JITAI should be recommended); and testing for heterogeneity across patients (ie, comparing the performance of a JITAI rule developed from data pooled across all participants to the performance of a rule learned from each participant’s individual trajectory of data).

Our experimental therapeutics model will be assessed by evaluating for associations between engagement with tools related to each therapeutic target (ie, behavioral activation, pain acceptance, and sleep quality), patient-reported improvement in the corresponding target (ie, clinical mediators), and subsequent improvement in distal clinical outcomes. We will also investigate whether and how these associations vary across patient characteristics, such as age, depression or anxiety severity, pain interference severity, and self-reported digital savviness.

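### Baseline-to-end change in PHQ-ADS cannot show the effectiveness of Wysa as a whole, and engagement measured after randomisation is listed as a moderator

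*Protocol article*

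**What the plan says.** **The effectiveness statement.** Under Outcomes, PHQ-ADS (PHQ-9 plus GAD-7) is the primary distal outcome. The section says that "analysis of changes in clinical outcomes from baseline to the final follow-up time point will not directly shed insight into the clinical effectiveness of each" of the adaptive interventions. In contrast, the same analysis "will provide insight into the effectiveness of the entire Wysa for Chronic Pain intervention as it is iteratively refined between randomized trials".

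**Who receives what.** The abstract states: "participants will all receive Wysa for Chronic Pain (by Wysa"; no arm goes without the app. Randomisation is to JITAIs or no JITAIs. Study Design and Setting says of the pilot: "The first trial will be a traditional 4-week, 2-arm randomized controlled trial". In each microrandomised trial (MRT), the "control arm will never receive JITAIs, regardless of whether they meet the prespecified criteria".

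**Who enters.** Participants must report "at least moderately severe depression or anxiety symptoms", defined as PHQ-9 or GAD-7 of at least 10. Concomitant Care places no restriction on other treatment.

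**The central hypothesis.** Goal of This Study states that "incorporating these JITAIs will increase engagement with Wysa for Chronic Pain by improving usability and, subsequently, will improve depression and anxiety symptoms".

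**The stated distal analysis.** Additional Analyses plans mixed-effects models of the distal outcomes at weeks 4, 8 and 12 to test moderation by participant characteristics and by "engagement with the Wysa app (ie, total dose, duration, and content) by including these as interaction terms". It does not say what the moderators interact with. The only between-group comparison the article describes, under Primary Outcome, is for proximal engagement.

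**The concern.** There are two separate problems.

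First, the effectiveness statement rests on change without a comparator. Since both arms use Wysa, the change mixes any effect of the app with regression to the mean, natural course and concurrent care. Comparing such changes between successive trials is not a randomised comparison either. Recruitment sources are left open (Ethical Considerations), refinements to the app unrelated to the JITAIs are expected (Study Design and Setting), and final follow-up is week 4 in the pilot but week 12 in the MRTs. Limitations mentions concomitant treatment, but neither the missing comparator nor regression to the mean.

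Second, engagement stands beside age, sex and baseline severity as a moderator. On the article's own hypothesis it lies on the path from JITAI to symptoms. People largely choose their own dose, so a model with arm and engagement compares groups that randomisation did not make comparable.

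At stake is what may be claimed from PHQ-ADS at the end. A fall in scores could be reported as effectiveness of Wysa, while the part of the hypothesis that the randomisation can test has no named analysis in the article.

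**Working it through.** **The plan's own figure.** No stated number is in dispute here. The pilot size reproduces: a two-sided 5% two-sample t-test with d = 0.8 and 80% power needs 25.5, so 26 per arm; 26/0.90 = 28.9, so 29. The same method is used in step 3.

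**1. Regression to the mean with no treatment effect.** From the article: entry if PHQ-9 or GAD-7 is at least 10; outcome is their sum. Assumed: source means of 8 to 12 (PHQ-9) and 6 to 10 (GAD-7), SDs 6 and 5.5, correlation 0.7 between the scales, test-retest correlation r of 0.6 to 0.8. Scores were simulated, rounded and limited to the scale ranges.

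| Source means (PHQ-9, GAD-7) | r | Mean baseline PHQ-ADS | Mean change | In baseline SD |
|---|---|---|---|---|
| 8, 6 | 0.6 | 22.8 | -3.43 | -0.52 |
| 8, 6 | 0.7 | 22.9 | -2.55 | -0.39 |
| 10, 8 | 0.7 | 24.6 | -1.93 | -0.27 |
| 12, 10 | 0.7 | 26.6 | -1.39 | -0.18 |
| 12, 10 | 0.8 | 26.5 | -0.91 | -0.12 |

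Hand check: expected fall ≈ (1 − r) × (mean of those selected − source mean). First row: 0.4 × (22.8 − 14) = 3.5. Last row: 0.2 × (26.5 − 22) = 0.9. Both agree closely with the simulation.

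With 109 participants (121 × 0.90, the first MRT), a pre-post test would be significant in 32% to 99% of trials, although nothing works. A change of source population alone also moves the result: at r = 0.7, 2.55 − 1.39 = 1.16 points between the first and last pair of source means.

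**2. Engagement in a model that contains arm.** Assumed: arm has no effect on symptoms Y; arm raises engagement E by g = 0.4 to 0.8 SD; a latent trait U drives both, with E = gA + 0.5U + error and Y = −0.5U + error (error variance 0.75 in each).

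- Engagement slope given arm: 0.5 × (−0.5)/1 = −0.25, although engagement does nothing.
- Arm coefficient given engagement: 0.25 × g, which is 0.10, 0.125 and 0.20 for g = 0.4, 0.5 and 0.8.
- Simulation with 68 v 41 participants: arm coefficient 0.102, 0.120 and 0.203 SD; arm significant in 8%, 9% and 16% of trials; engagement significant in 35% to 38%; interaction significant in about 5%.

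The bias is thus in the arm and engagement main effects. The interaction term kept its nominal error rate in this simple set-up.

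**3. What the concurrent randomised contrast can detect.** Two-sided 5%, 80% power, two-sample t-test, no gain from baseline adjustment counted.

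| Attrition | Pilot, 29 v 29 | MRT 1, 75 v 46 | MRT 2, 120 v 55 | MRTs 1 and 2, stratified by trial |
|---|---|---|---|---|
| 10% (article, for engagement) | 0.79 | 0.56 | 0.48 | 0.36 |
| 20% (assumed) | 0.84 | 0.59 | 0.51 | 0.38 |
| 40% (assumed) | 0.98 | 0.69 | 0.59 | 0.44 |

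Check for MRT 1 by the normal approximation: 2.80 × √(1/67.5 + 1/41.4) = 0.55. The article's 10% refers to automatically recorded engagement; questionnaire loss may be larger, hence the other rows. Pilot controls are followed for 4 weeks, so they cannot enter a week-12 contrast.

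**The case against.** The case for leaving the plan alone has substance. The project is called formative, Outcomes promises only insight and disclaims clinical inference for each JITAI, and effectiveness is assigned to a later hybrid trial. Every trial has a control arm, partly to account for time-varying factors. With one entry rule throughout, regression to the mean is largely shared by the arms and, if recruitment stays stable, by successive trials. Changes in concomitant care are recorded. An analysis linking engagement, mediators and outcomes is already planned.

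Most of this limits the point without removing it. The disclaimer covers single JITAIs, and the same sentence then claims effectiveness for the whole. Using the control arm to remove time trends also subtracts Wysa, because controls receive it; what remains is the effect of the JITAI package. Stable recruitment is not assured.

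Three stronger readings are tempting and are not supported:

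- *That effectiveness will be concluded from the engagement models.* Additional Analyses presents them only as moderation tests; the effectiveness remark stands elsewhere and does not mention engagement.
- *That 12-week total dose will explain week-4 and week-8 scores.* The article gives no time window for engagement, and Table 4 schedules engagement at several visits, so dose up to each visit could be used.
- *That the plan omits an arm comparison of PHQ-ADS.* The article names none, but moderation by interaction may imply an arm term, and a fuller model may stand in an analysis plan not shown.

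**Conclusion.** The point holds in two limited parts.

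1. Baseline-to-final change cannot inform the effectiveness of Wysa as a whole. This follows from the design and needs no assumption: no arm lacks Wysa, so no later model can supply the comparator. The size does rest on assumptions: about 0.1 to 0.5 baseline SD of apparent improvement from the entry rule alone, before any concurrent care.
2. Engagement measured after randomisation should not be treated as a moderator alongside baseline characteristics. If the model also contains arm, the arm main effect can be wrong by about 0.1 to 0.2 SD and engagement can appear effective when it is not. These figures depend on an assumed shared trait and an assumed effect of arm on engagement. Inflation of the interaction test was not shown.

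The randomised contrast can address the clinical part of the central hypothesis, but for moderate effects only, and it cannot stand in for the effect of Wysa. The proximal engagement outcomes are untouched by this point.

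**What to change.** 1. **Outcomes.** Reword the sentence so that PHQ-ADS change within arms and between trials is descriptive and is not said to inform the effectiveness of Wysa.
2. **Distal analysis.** Name the concurrent randomised contrast, with versus without JITAIs, as the test of the clinical part of the hypothesis: PHQ-ADS at week 4 in the pilot and at weeks 4, 8 and 12 in each MRT, in all randomised participants of that trial, by a mixed model adjusted for baseline PHQ-ADS. State that it estimates the JITAI package and not Wysa as a whole, and give the detectable effects (d about 0.56 in the first MRT and 0.48 in the second with 10% attrition; larger with more questionnaire loss).
3. **Additional Analyses.** Keep only baseline characteristics as moderators. Examine engagement accrued before each outcome in the mechanism analysis already planned, and label it observational.

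The cost is wording and routine analysis of data already being collected; no extra participants or visits are needed. The price is a more modest clinical claim and an arm contrast with limited power.
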